### Interventions

In total, 24 intervention sessions will be delivered 3 times a week over 8 weeks. Intervention therapists will undergo standardized training and a structured intervention log with the 3 aspects of the EP, and the respiratory training outlined will be followed each session to assure intervention fidelity.

### EP Components

Both groups will participate in the EP consisting of 3 components recommended by American Heart Association (AHA) poststroke exercise recommendations [27], directed by the intervention physical therapist, and individualized to the participants’ ability.

#### Strengthening Exercise

Resistance exercises will address primary muscle groups of the upper and lower limbs and trunk. Graded resistance will be provided through weight machines or resistance bands.

In terms of progression, the ability to perform an exercise with appropriate kinematics will determine initial resistance. Once the participant can perform 2 sets of 10 repetitions, resistance will be increased.

#### Cardiovascular Exercise

Exercise modalities may include treadmill, recumbent cross trainer, recumbent bicycle, stairs, elliptical stepper, upper-extremity ergometer, arc trainer or provided through overground gait, sit-to-stand repetitions, shallow knee bends, step-ups, and marching in place.

In terms of progression, participants will wear a heart rate monitor and exercise between 40% and 70% of heart rate reserve. The exertion will be subjectively reported using the rate of perceived exertion scale [28]. Progression will occur by increasing exercise duration, resistance, or speed.

#### Flexibility Exercise

Static stretching of the trunk and upper and lower extremities, 2 repetitions of each stretch held for 20 seconds. Muscles groups will be individualized according to participants’ needs.

### Respiratory Training

Participants will be randomized to the RST or RRT group.

#### RST Group

RST will consist of a bout of inspiratory strength training at the start of each EP session, plus a bout of expiratory strength training at the conclusion of each EP session. RST devices (Orygen Dual Valve, Forumed SL) provide up to 70 cm H_2_O of inspiratory and 80 cm H_2_O of expiratory pressure threshold loads. RST bouts include 5 sets of 5 maximal volume and speed breaths of both inspiratory and expiratory muscle training 2 times during each session. The initial intensity will be 25% of the maximal inspiratory and expiratory pressures the subject can generate. In terms of progression, the inspiratory setting of the training device will be increased up to 10% of the training load from the first set each session, to achieve a rate of perceived exertion of 6-8 (Modified 10-point Borg scale) [29] with complete valve opening. Expiratory settings will be progressed similarly.

#### RRT Group

RRT will consist of bouts of relaxation breathing at the start and conclusion of each EP session. Participants will be guided to breathe slowly through a respiratory training device (Threshold PEP, Respironics), with minimal resistance. RRT bouts include 5 sets of 5 breaths, 2 times during the session. While the effects of relaxation breathing exercises may include a modest lowering of systolic blood pressure in some hypertensive patients [30], this group serves as an active control. In terms of progression, there will be no progression for this group.

### Outcome Measures

Participants will be assessed (1) at baseline, (2) after 12 sessions, and (3) after 24 sessions by a physical therapist blinded to group assignment. Blinded assessors will undergo standardized training to assure assessment fidelity. Following intervention completion participants will complete monthly health status questionnaires.

#### Primary Objective Outcomes

The World Health Organization’s International Classification of Functioning, Disability, and Health model [31] recognizes that functioning and disability as a result of a health condition (stroke, in this trial) are multidimensional concepts, relating not simply to impairment at the level of one’s body (ie, muscle strength) but to limitations in activity one might experience, as well as one’s restrictions in societal participation. To assess more broadly how addressing respiratory muscle weakness can improve quality of life after stroke, we will examine outcomes across these dimensions (Figure 2).

**Figure 2 figure2:**
[figure not shown]
Outcome measures across World Health Organization’s International Classification of Functioning, Disability and Health model. 5XSTS: Five Times Sit to Stand; 6MWT: Six Minute Walk Test; FACIT-D: Functional Assessment of Chronic Illness Therapy – Dyspnea; FACIT-F: Functional Assessment of Chronic Illness Therapy – Fatigue; FEV1: Forced Expiratory Volume in 1 second; FSS: Fatigue Severity Scale; FVC: Forced Vital Capacity; MEP: Maximum Expiratory Pressure; MIP: Maximum Inspiratory Pressure; Neuro-QOL: Neuro Quality of Life; PCF: Peak Cough Flow; PHQ-9: Patient Health Questionnaire -9; PROMIS-10: Patient-Reported Outcomes Measurement Information 10; SIS-P: Stroke Impact Scale – Participation; WHO-QOL BREF: World Health Organization Quality of Life Brief Version.

Our primary outcome is maximum inspiratory pressure (MIP). MIP is a measure of the strength of inspiratory muscles, primarily the diaphragm [32]. Participants will perform a seated MIP maneuver using a respiratory pressure manometer, from residual volume, in accordance with American Thoracic Society testing guidelines for respiratory muscle testing [33]. Additional respiratory measures include maximal expiratory pressure (measure of the strength of expiratory muscles, primarily the abdominals and intercostals) [33], forced vital capacity (the total volume of air blown out of the lungs during forced exhalation after maximal inspiration) [33], forced expiratory volume in 1 second (a measure of the amount of air that can be forced out of the lungs in one second following a full inhalation) [33], and peak cough flow (maximum expiratory flow during the compressive phase of a cough) [34]. Open circuit spirometry will provide breath-by-breath cardiopulmonary data while participants complete the 6-minute walk test [35]. Additional measures of physical function include the 5-times sit-to-stand test [36] and spatiotemporal gait characteristics captured while walking across an instrumented walkway. Steps per day and GPS data will be obtained at baseline and intervention conclusion for 1 week. A portable accelerometer will record participants’ steps, and a GPS device will record location. A walk score [37,38] and an area deprivation index [39] score will objectively characterize the “walkability” and the socioeconomic status of the participant’s neighborhood.

Finally, self-report measures of participation and quality of life will also address our primary objective. These include the Participation subsection of the Stroke Impact Scale [40]; the abbreviated World Health Organization Quality of Life instrument [41], which measures the domains of physical health, psychological health, social relationships, and environment; the Functional Assessment of Chronic Illness Therapy Dyspnea [42] and Fatigue [43] Scales; the Fatigue Severity Scale [44]; the Patient Health Questionnaire-9 depression assessment [45]; the Patient Reported Outcomes Measurement Information-10, an assessment of health status after stroke [46]; and the satisfaction and ability to participate in life roles subscales of the Neuro Quality of Life [47] (Table 1).

**Table 1 table1:** Outcome measures.

Assessment	Outcome measured	Time to complete	Scoring	Psychometrics
MIP^a^	Maximum pressure created during inspiration measured with a manometer	8 minutes	Pressure measured in cm H_2_O	Reliability [48] Validity [48]
MEP^b^	Maximum pressure created during expiration measured with a manometer	8 minutes	Pressure measured in cm H_2_O	Reliability [48] Validity [48]
PCF^c^	Strength of cough	5 minutes	Liters of air breathed out per minute; L/min	Reliability [49] Validity [49]
FVC^d^	Maximum amount of air exhaled after fully inhaling and making a maximal effort.	5 minutes	Volume measured in liters	Reliability [50,51] Validity [50,51]
FEV_1_^e^	The volume of air exhaled in the first second during forced exhalation after maximal inspiration	1 minute	Volume measured in liters	Reliability [50,51] Validity [50,51]
6MWT^f^	Participants walk for six minutes covering as much ground as possible. Participants were permitted to stop and rest at any time during the test.	6 minutes	Distance measured in meters	Reliability [52] Validity [53]
5XSTS^g^	Participants stand up and sit down from a 16” solid seat as quickly as possible 5 times, with their arms folded across their chest.	1 minute	Time is measured in seconds	Reliability [54] Validity [54]
Steps/day	Number of steps taken over a seven-day period measured with an activity monitor	7 days	Number of steps completed each day	Reliability [55] Validity [56]
PHQ-9^h^	Self-report questionnaire to assess depressive symptoms	6 minutes	Nine items scored on a 0-3 Likert scale	Reliability [57] Validity [57]
SIS-P^i^	Self-report questionnaire to assess ability to participate in meaningful life activities	3 minutes	Eight items scored on a 1-5 Likert scale	Reliability [58] Validity [58]
WHO-QOL BREF^j^	Self-report questionnaire to assess four QOL domains: physical health, psychological health, social relationships, and environment.	12 minutes	26 items rated on a 5-point Likert scale. Each domain score is transformed into a scaled score, with a higher score indicating a higher QOL.	Reliability [59] Validity [59]
FSS^k^	Self-report questionnaire to assess the impact of fatigue on life and functional activities	8 minutes	Nine items scored on a 1-7 Likert Scale; one item scored on a 0-10 visual analog scale.	Reliability [60] Validity [60]
FACIT-D^l^	Self-report questionnaire to assess dyspnea severity during activities of daily living	5 minutes	Ten items scored on a 0-3 Likert scale	Reliability [42] Validity [42]
FACIT-F^m^	Self-report questionnaire to assess fatigue experience and impact on daily life	5 minutes	Thirteen items scored on a 0-4 Likert scale	Reliability [61] Validity [61]
Neuro-QOL^n^	Two self-report questionnaire subscales to assess 1) the Ability to Participate in Social Roles and Activities and 2) Satisfaction with Social Roles and Activities	10 minutes	A total of 16 items scored on a 1-5 Likert scale	Reliability [47] Validity [47]
PROMIS-10^o^	Self-report questionnaire to assess multiple domains of health	5 minutes	Ten items scored on a 1-5 Likert scale	Reliability [62] Validity [62]

^a^MIP: maximum inspiratory pressure.

^b^MEP: maximum expiratory pressure.

^c^PCF: peak cough flow.

^d^FVC: forced vital capacity.

^e^FEV1: forced expiratory volume in 1 second.

^f^6MWT: 6-Minute Walk Test.

^g^5XSTS: Five Times Sit-to-Stand.

^h^PHQ-9: Patient Health Questionnaire-9.

^i^SIS-P: Stroke Impact Scale–Participation.

^j^WHO-QOL BREF: World Health Organization Quality of Life Brief Version.

^k^FSS: Fatigue Severity Scale.

^l^FACIT-D: Functional Assessment of Chronic Illness Therapy–Dyspnea.

^m^FACIT-F: Functional Assessment of Chronic Illness Therapy–Fatigue.

^n^Neuro-QOL: Neuro Quality of Life.

^o^PROMIS-10: Patient-Reported Outcomes Measurement Information 10.

#### Secondary Objective Outcomes

To investigate if RST in the chronic poststroke period impacts the rate of respiratory complications, we will follow participants for 1 year after intervention. Respiratory complications will be defined as the onset of respiratory symptoms that require the evaluation and treatment by a medical provider or hospitalization for respiratory causes. If the participant reports a respiratory complication, medical records will be obtained and a blinded assessor will review the record to confirm diagnosis.

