**Methods:**

This study will be a randomized controlled trial. Participants are 80 community-dwelling adults with chronic stroke. In conjunction with a 24-session (3 times/week for 8 weeks), American Heart Association–informed, whole-body exercise program, participants will be randomized to receive either respiratory strength training or respiratory relaxation training. Study intervention will be directed by a physical therapist and take place in a community fitness center. Outcome assessments will occur in a clinical research center. The primary outcome measure is maximal respiratory pressure. Secondary outcome measures include airway clearance, walking endurance, spatial-temporal gait characteristics, community walking, functional strength and fatigue, depression, and societal participation measures. Longer-term societal participation is a complex domain that may be influenced by other factors beyond physical function. Participants’ health status will be monitored for 1 year following the intervention for falls, respiratory illness, and hospitalizations. Additional subanalyses will evaluate the effect of smoke exposure on short- and long-term outcomes. Outcome assessors are blinded to group assignments. Respiratory relaxation training is an active comparator, but no pure control group is included.

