### Study Objective and Aims

The primary objective of this trial is to test the hypothesis that a combined EP with RST improves physiologic, activity, and societal participation outcomes in chronic stroke survivors. In addition to limb and respiratory weakness, up to 78% of patients after stroke present with dysphagia [6], a significant risk factor for aspiration. Cough is a critical mechanism to guard against aspiration and is often impaired after stroke [7], resulting in greater incidences of aspiration and chest infection [8,9]. Furthermore, pneumonia is the leading cause of nonvascular death in acute [10] and chronic [11] phases after stroke. RST could improve airway clearance as a protective function. The adoption of interventions capable of preventing the occurrence of respiratory complications may substantially improve the long-term outcomes of these patients [12]. Several small-scale studies have demonstrated that inspiratory [13-16] and expiratory [14] muscles respond to strength training in patients after stroke, but the impacts of respiratory strengthening on function are less clear. In a systematic review of poststroke respiratory muscle training randomized controlled trials, Menezes et al [17] reported there were insufficient data to determine whether the benefits of respiratory muscle training are realized in gains in functional activity level or participation, concluding that future trials are needed to assess the effects of training on one’s activity and participation in life roles. RST for individuals after stroke has the potential to facilitate a return to these important societal roles.

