Our secondary objective is to prospectively monitor health status for 1-year following the exercise intervention. There is a clear link between the presence of respiratory dysfunction in individuals after stroke and the incidence of respiratory complications such as aspiration or respiratory infections [18-20]. Menezes et al [17] revealed that respiratory muscle training reduced the relative risk of respiratory complications immediately and 6 months after the commencement of the intervention. Others have reported that expiratory muscle strength training exercises improve respiratory strength, cough, and swallowing function in stroke [21-23]. A 2016 meta-analysis [17] revealed that respiratory muscle training reduced the relative risk of respiratory complications immediately and 6 months after the commencement of the intervention. However, this conclusion was based on just 2 trials, and procedures for detecting the occurrence of respiratory complications were not sufficiently robust.

An exploratory objective will evaluate potential differential responses to respiratory muscle training based on smoke exposure. Cigarette smoking negatively impacts respiratory health and increases the risk of cardiovascular events. While direct cigarette smoking is a known risk factor for stroke and poststroke complications, individuals exposed to secondhand smoke also face high health risks. There is a strong, dose-dependent association between passive smoking and stroke [24].

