### Randomization, Allocation, and Blinding

Participants will be randomized to the EP plus RST group or EP plus respiratory relaxation training (RRT group) using the Microsoft Excel (Microsoft Office Professional Plus 2016) *RAND* function. Participants and the intervention physical therapist will be aware of the group assignment due to the nature of the intervention; however, study evaluators will remain blinded.

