### Limitations

We recognize some limitations of the study design. The study was powered to distinguish the 8-week effects of RST from RRT on MIP. We acknowledge that societal participation is multidimensional, and longer-term changes may be influenced by many contributing factors beyond respiratory strength and walking endurance [77,78]. The use of patient-reported outcome measures and assessment of the Area Deprivation Index will help identify some factors that contribute to societal participation. Since group assignment will be based on the type of respiratory training, it is possible there may be unequal proportions of smoke-exposed and nonsmoking participants in each group. The monitoring of smoke exposure will enable us to explore whether the combined respiratory and whole-body exercise approaches offer distinct benefits to cigarette smoke-exposed individuals. While study assessors will be blinded to group assignment, patients and exercise supervisors will know their respiratory exercise assignment. A true control or “sham” respiratory training intervention was not included; rather, the RRT serves as an active comparator. The volume of respiratory exercises during exercise sessions will be the same for both groups, even though the physiological effects of RST and RRT exercises likely differ.

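### Blinded record review of respiratory complications starts only from an unblinded participant's report, and the hospitalizations and adverse events also collected are not stated to reach that review

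*Protocol article*

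**What the plan says.** All places are in the protocol article.

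- **Definition** (Secondary Objective Outcomes): "Respiratory complications will be defined as the onset of respiratory symptoms that require the evaluation and treatment by a medical provider or hospitalization for respiratory" reasons.
- **Trigger and confirmation** (same section): "If the participant reports a respiratory complication, medical records will be obtained and a blinded assessor will review the record to confirm diagnosis".
- **Follow-up instrument** (Outcome Measures): "Following intervention completion participants will complete monthly health status questionnaires". Trial Design sets the period at 1 year.
- **Who is blinded** (Randomization, Allocation, and Blinding): "Participants and the intervention physical therapist will be aware of the group assignment due to the nature of the intervention". Evaluators stay blinded. Limitations repeats that "patients and exercise supervisors will know their respiratory exercise assignment".
- **What else is collected**: the Methods part of the Abstract says health status will be "monitored for 1 year following the intervention for falls, respiratory illness, and hospitalizations", with no restriction of hospitalizations to respiratory causes. Ethical Considerations has all adverse events up to 12 months after the intervention reported to the institutional review board.
- **Why detection matters to the authors** (Study Objective and Aims): of the earlier evidence on this outcome they write that "procedures for detecting the occurrence of respiratory complications were not sufficiently robust".

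**The concern.** The assessor is blinded, but an unblinded person decides which events the assessor sees. Review that serves to confirm a reported diagnosis protects specificity. It does nothing for sensitivity, and sensitivity is where knowledge of the assigned arm can act. Take a participant admitted after a fall whose hospital record shows pneumonia, and who reports the fall but no respiratory complication. The trial would know of the admission, yet the stated rule would not send the record to the assessor.

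The outcome carries the secondary objective, and Anticipated Findings states a directional hypothesis for it: fewer adverse respiratory events with RST. Few events are expected, so a small difference between arms in what participants label respiratory could create, enlarge or hide an apparent effect.

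**Working it through.** The article states no power or precision for the 1-year outcome, so there is no figure of its own to reproduce. The check is in three parts.

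**1. Which events reach the blinded assessor under the stated text**

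| Event | Known to the trial? | Stated to go to blinded review? |
|---|---|---|
| Participant reports a respiratory complication | Yes | Yes (Secondary Objective Outcomes) |
| Hospitalization reported, not called respiratory | Yes (Abstract, Methods) | No |
| Adverse event or death to 12 months, not reported as respiratory | Yes if recorded as an adverse event (Ethical Considerations) | No |
| Treated outpatient visit, not called respiratory | Not stated | No |

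The second and third rows are the gap: the information is collected, but the link to adjudication is not stated.

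**2. Expected number of events (illustrative)**

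Inputs from Power Calculations: a 70% lower lung infection rate, a number needed to treat of 7, and 40 participants per group.

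- Risk difference = 1/7 = 0.143.
- Control risk = 0.143 / 0.70 = 0.204.
- RST risk = 0.30 × 0.204 = 0.061.
- Expected participants with an event: 40 × 0.204 = 8.2 and 40 × 0.061 = 2.4.

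These inputs come from a subacute stroke study. The same section says that the effect in chronic stroke is not yet known.

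**3. Effect of incomplete reporting (reporting rates are assumptions)**

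Observed risk = true risk × probability that the event is reported as respiratory. With no true effect, the true risk cancels, so apparent risk ratio = reporting in RST / reporting in RRT, whatever the base rate.

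| Reporting RST | Reporting RRT | Apparent risk ratio | Observed events at true risk 0.204 (RST vs RRT) |
|---|---|---|---|
| 0.9 | 0.9 | 1.00 | 7.3 vs 7.3 |
| 0.8 | 0.9 | 0.89 | 6.5 vs 7.3 |
| 0.7 | 0.9 | 0.78 | 5.7 vs 7.3 |
| 0.6 | 0.9 | 0.67 | 4.9 vs 7.3 |

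Reversing the arms gives 0.9/0.8 = 1.13, 0.9/0.7 = 1.29 and 0.9/0.6 = 1.50.

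Equal under-reporting leaves the risk ratio unbiased but costs power. For a two-sided 5% comparison of proportions at 40 per arm (pooled variance under the null), the true risks 0.204 and 0.061 give power of about 0.47 with complete reporting. With equal reporting of 0.9, 0.8, 0.7 and 0.6, power is 0.42, 0.38, 0.34 and 0.29.

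Single events also count. With a true 2 vs 8 the risk ratio is 0.25. Missing one RST event gives 1/8 = 0.125; missing one RRT event gives 2/7 = 0.29. The first exaggerates the effect and the second dilutes it.

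**The case against.** **The events are not necessarily lost.** A reader might infer that mislabelled hospitalizations and fatal respiratory events disappear from the trial. The document does not support that. Hospitalizations in general are monitored, and adverse events to 12 months are reported, so such an event may well be on file. What stands is that no text sends it to the blinded assessor or into the endpoint.

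**Death may already be covered.** A reader might also infer that the endpoint leaves out fatal events, given the statement that "pneumonia is the leading cause of nonvascular death in acute [10] and chronic [11] phases after stroke". But a fatal pneumonia that was treated or led to admission already meets the definition. Proxy reporting and the handling of unreturned questionnaires are details that an article commonly leaves to the full protocol. Their absence is no finding.

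**The questionnaire is not shown.** It may ask about symptoms, visits and admissions, with staff classifying the answers. That is possible, but the article describes its ascertainment rule and names a participant's report of a respiratory complication as the trigger. The point rests on that stated rule.

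**The bias mechanism is partly assumed.** Participants know their arm, but the article does not say what they were told about protection of the lungs. Both arms do the same volume of device breathing. Requiring provider care and blinded confirmation also ties the endpoint to documented events. This limits what can be said about direction and size; it does not close the route.

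**The authors' criticism of earlier trials is general.** It does not name self-report triggering as the defect. It shows only that they regard detection as important for this outcome.

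**Conclusion.** The point holds in a limited form. The only trigger stated for obtaining and blind-reviewing records is a report by a participant who knows the assignment, and the broader data already collected are not stated to be adjudicated. The 1-year comparison is therefore open to differential ascertainment that the blinded step cannot correct.

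The document fixes neither the direction nor the size. The apparent risk ratios of 0.89 to 0.67, or 1.13 to 1.50 in reverse, rest on assumed reporting rates. The count of about 8 vs 2 rests on subacute stroke figures. What does not depend on those assumptions is the structure: the filter works in one direction, and no text links the other two data streams to it. The point concerns the secondary objective only and leaves the primary outcome, maximum inspiratory pressure, untouched.

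**What to change.** Amend the trigger in Secondary Objective Outcomes as follows:

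- Obtain records for every hospitalization reported during the follow-up year, and for every adverse event or death already known to the trial, whether or not the participant calls it respiratory.
- Have the same blinded assessor decide whether each one meets the respiratory-complication definition, and state that death from a respiratory cause counts as an event.
- Keep the present trigger, reported respiratory symptoms, for outpatient visits. Requesting records for every treated visit of any cause would be a much larger task, and the Abstract does not list such visits among the events monitored.

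The cost is an amendment to one paragraph and a modest number of extra record requests through the existing process and assessor. Results reports 69 participants enrolled by July 2024, so applying the rule uniformly means retrospective requests for those already followed, where consent permits. The consent form is not shown, so this needs checking. Outpatient events that participants do not recognise as respiratory would remain undetected, and the report of results should say so.
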